#### Nutritional intake questionnaire

The last twelve months’ retrospective means of calculation will be the basis for evaluating habitual dietary consumption. We will employ a Food Frequency Questionnaire (FFQ) that was previously validated using information from the Hong Kong Adult Dietary Survey [33].

#### Sunlight exposure questionnaire

This study will employ the Chinese version of the Sunshine Exposure Questionnaire, which is a reliable tool for measuring lifetime solar exposure among Chinese women in Hong Kong [34].

#### Serum myokine evaluation

Blood taking (5 ml) will be performed. After centrifugation, the serum will be stored in a -80º freezer until needed. The Human Myokine Magnetic Bead Panel (Millipore) with Bioplex-200 bead-based suspension assay system (LKSIHS core facilities) or enzyme-linked immunosorbent assay (ELISA) will be used for the quantitative investigation of myokines and proteins relevant to muscle metabolism. These include Brain-derived neurotrophic factor (BDNF), Fibroblast growth factor-21 (FGF-21), Interleukin-6 (IL-6), IL-15, Irisin, Insulin-like growth factor 1 (IGF-1), FGF-2, IL-8, Follistatin, Musclin, Myonectin, Decorin, Meteorinlike, Osteopontin, Secreted protein acidic and rich in cysteine (SPARC), Klotho, Procollagen type III N-terminal peptide (P3NP), and C-terminal of troponin T1 (TNNT1).

#### Serum vitamin D assays

A commercial 25(OH) Vitamin D ELISA kit (Abcam ab213966) will be used to assess the serum 25(OH)Vit-D levels in accordance with the manufacturer’s instructions. This will yield a quantitative result of 25(OH) Vitamin D3 and 25(OH) Vitamin D2. 1.98 ng/ml of sensitivity (range: 0.5 ng/ml to 1010 ng/ml). When baseline serum 25(OH)D levels are less than 30 ng/mL, it is considered as vitamin D insufficiency [35].

### Data management and confidentiality

To guarantee the accuracy of outcome evaluations and data collection, a research assistant will get training. Any problems affecting the quality of research will be monitored by the ethics committee, and appropriate action will be taken if required. Patients may drop up the research at any moment, for any reason, and it won’t have an impact on their legal or medical rights. An identity code will be given to every patient. The database and list of patient identifying codes will be protected.

### Data access

The cleansed data sets will be made available to all Principal Investigators. Each and every data set will have a password. Data distributed to project team members will be blinded of any participant identifying information in order to maintain confidentiality.

### Data statement

The results will be presented at international scientific conferences and through publications in peer-reviewed journals.

### Plans for collection, laboratory evaluation and storage of biological specimens for genetic or molecular analysis in this trial/future use

Blood will be taken for analysis. Once the sites have been delivered to the local research facility, the samples will be collected, stored, and processed in compliance with local protocols. Blood shall be stored between 2 and 8°C before being treated in the designated time. Every sample collected for the research will have a patient identification code attached; otherwise, no personally identifying information will be included. Patients have the option to consent to the preservation of their samples in case they are needed for additional research.

Samples will be anonymously stored at a central location for a minimum of five years and a maximum of 10 years after the research is completed. Following that, they will be burned to ashes in compliance with regional customs and laws. The potential use of the stored samples is mentioned in the informed consent form. Any further use of the documents, nevertheless, will require approval from the institutional ethics council.

### Sample size calculation

Based on our power calculation, we aim to recruit 28 patients for both groups, with a total of 56 participants. Quadriceps muscle strength measured by the handheld dynamometer will be the primary outcome for sample size estimation. The effect size of the isometric quadriceps muscle strength has been determined as 0.34 in patients with knee OA [36]. A repeated-measures one-way analysis of variance (ANOVA) will be used to compare knee muscle strength, muscle mass, physical functional test, biomarkers, and questionnaire score for four timepoints (before the vitamin D supplementation (Baseline), at 3months, 6 months, and 12 months after the commencement of vitamin D supplementation). When the sample size is 23 per group with 4 repeated measurements, will have 80% of the power to detect at the 0.05 significance level. An additional 20% will be added to account for possible attrition. Thus, our sample size of 28 participants per group (total *n* = 56) will be sufficient to achieve our objective. The sample size was calculated using G*Power 3.0 software.

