### Statistical analysis

Data in this study will be analyzed according to the intention-to-treat principle. Only the full analysis set and per-protocol set will be used for primary outcome analysis. The last observation carried forward (LOCF) will be used to impute the missing data by replacing it with the last observed value.

Quantitative variables will be expressed as mean ± standard deviation. Normality tests will be performed to determine whether the data is normally distributed. A one-way analysis of covariance (ANCOVA) tests with Bonferroni correction and with the baseline value as a covariate was conducted at 3m,6m, and 12m to determine the group effect on each parameter. Independent T-test (two-tailed) are used for multiple testing of continuous variables. Whereas the Chi-square test will be used to compare the proportions of categorical variables and to calculate the differences in the count data. A repeated measure analysis of variance (ANOVA) will be used to analyze the trend of changes in the scores among four-time points (Baseline, 3m, 6m, 12m) to determine the group×time effects. Post hoc analysis with Bonferroni correction will be conducted to explore the differences between baseline and 3m, baseline and 6m, 6m and 12m. The statistical analysis will be performed using commercialized statistical software (SPSS, version 29.0, IBM). All statistical significance is defined as P < 0.05.

Additional analyses will include subgroup analyses to estimate treatment effects for both female and male participants, normal BMI and overweight or obese participants.

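### The 80% power claim gives neither the metric of 0.34, the correlation nor the effect tested, and is not shown for the Bonferroni-corrected ANCOVA that tests the group effect

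*Protocol article*

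**What the plan says.** In the protocol article, the section Sample size calculation takes quadriceps strength as the outcome for sizing and states: "The effect size of the isometric quadriceps muscle strength has been determined as 0.34 in patients with knee OA". The analysis it names is this: "A repeated-measures one-way analysis of variance (ANOVA) will be used to compare knee muscle strength", with other outcomes, over baseline, 3, 6 and 12 months. The claim follows: "When the sample size is 23 per group with 4 repeated measurements, will have 80% of the power to detect", "at the 0.05 significance level". The 23 per group are raised to 28 for attrition, and G*Power 3.0 is cited. The section does not say whether 0.34 is Cohen's f or a standardised mean difference. It also does not give the correlation between visits, or say whether the calculation concerns a group, time or group-by-time effect.

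The section Statistical analysis gives the group effect on each parameter to one-way ANCOVA: "tests with Bonferroni correction and with the baseline value as a covariate was conducted at 3m,6m, and 12m". It also says "Independent T-test (two-tailed) are used for multiple testing of continuous variables". The repeated-measures ANOVA over the four timepoints is there to determine the group-by-time effect. The general rule is "All statistical significance is defined as P < 0.05".

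**The concern.** A power statement means something only for a named test, effect scale and alpha. Here the scale and the effect are missing, and the alpha is plain 0.05 although the stated test of the group effect carries a Bonferroni correction. The reading that best reproduces 23 per group is a test to which the analysis section gives no role. That test averages the arm difference over four visits, one of them baseline, where randomisation makes the expected difference zero.

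The sample size section concludes that the sample is sufficient for the trial's objective. If that is not so for the test that will be reported, a null result could be read as evidence of no effect from a trial believed to have 80% power.

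**Working it through.** **Inputs from the protocol.** Effect size 0.34; 23 per group (N = 46); m = 4 measurements; alpha 0.05; 1:1 allocation; 28 per group recruited.

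**Assumptions.** Correlation r between visits is not stated; 0.5 is used, with a range of 0.3 to 0.8. Variances are equal with compound symmetry. The Bonferroni divisor is not stated; 3 is used, for the three visits.

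**1. Reproducing the stated figure.** For the group main effect in a repeated-measures ANOVA, lambda = f² × N × m / (1 + (m − 1)r), on 1 and N − 2 degrees of freedom.
- f = 0.34, r = 0.5: lambda = 0.1156 × 46 × 4 / 2.5 = 8.51, power 0.814.
- N = 44: lambda = 8.14, power 0.796. So 46 is the smallest even total that reaches 80%.

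For two equal groups d = 2f, so f = 0.34 is a difference of 0.68 SD, held at all four visits.

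**2. Other readings of 23 per group.**
- Group-by-time with f = 0.34, lambda = f² × N × m / (1 − r), r = 0.5: N = 14 suffices, and power at N = 46 is above 99%.
- Group-by-time with 0.34 as a standardised mean difference (f = 0.17): power 0.776 at N = 46 and minimum N = 50 at r = 0.5. At r = 0.53 the minimum is also 46 (power 0.803).
- Group main effect with f = 0.17, r = 0.5: power 0.297 at N = 46, minimum N = 172.

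The first calculation is the best match because it needs only the round value 0.5, but it is not the only possible one.

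**3. Power of the planned tests for 0.68 SD.** ANCOVA at one visit: noncentrality = d / √(1 − r²) × √(n/2), on 2n − 3 degrees of freedom, two-sided. At r = 0.5 and n = 23 this is 0.68 / 0.866 × 3.391 = 2.66. Group-by-time, with no difference at baseline and d at each later visit: lambda = (N/4) × Σ(d_t − mean d)² / (1 − r), on 3 and 3(N − 2) degrees of freedom. The deviations are −0.51 once and 0.17 three times, so the sum of squares is 0.3468. At r = 0.5 and N = 46, lambda = 11.5 × 0.3468 / 0.5 = 7.98.

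| n per arm | r | ANCOVA at 0.05 | ANCOVA at 0.05/3 | Group-by-time, sustained |
|---|---|---|---|---|
| 23 | 0.3 | 66% | 48% | 48% |
| 23 | 0.5 | 74% | 57% | 64% |
| 23 | 0.7 | 88% | 77% | 87% |
| 23 | 0.8 | 96% | 91% | 97% |
| 28 | 0.5 | 82% | 68% | 74% |
| 28 | 0.7 | 94% | 86% | 93% |

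The two-sample t-test at 0.05 has 62% with 23 per arm and 71% with 28. The averaged main effect itself falls from 81% to 57% (23 per arm, r = 0.5) once the baseline difference is set to zero: the mean difference is 0.75 × 0.68 = 0.51, so f = 0.255 and lambda = 0.0650 × 46 × 4 / 2.5 = 4.79.

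**4. If 0.34 is a standardised mean difference.** With 23 per arm, ANCOVA power at r = 0.3, 0.5 and 0.7 is 22%, 26% and 35% at 0.05, and 11%, 13% and 20% at 0.05/3.

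**5. Difference detectable with 80% power.** Solving the ANCOVA formula for d:

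| n per arm | r | At 0.05 | At 0.05/3 |
|---|---|---|---|
| 23 | 0.5 | 0.73 SD | 0.86 SD |
| 23 | 0.7 | 0.60 SD | 0.71 SD |
| 28 | 0.5 | 0.66 SD | 0.77 SD |
| 28 | 0.7 | 0.55 SD | 0.64 SD |

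**The case against.** The strongest reply is that metric, correlation and G*Power routine are inferred from a numerical match, and an article may leave such settings to the full protocol. This stands as to which routine was used: group-by-time with f = 0.17 also gives 46 at a correlation of 0.53, and that is the effect for which the repeated-measures ANOVA is planned. It does not rescue the power claim, which the article makes in its own right and which is not shown for the corrected ANCOVA under either reading.

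Four stronger conclusions are tempting, and the protocol does not support them.
- A reader might infer that the powered test is never run, or that the analysis has no arm factor because it is called one-way. The planned two-group repeated-measures ANOVA yields a group main effect as a by-product, and the same section speaks of sizes per group; the label is loose.
- A reader might infer that every planned test falls short. Uncorrected ANCOVA passes 80% with 23 per arm at correlation 0.6 (80.4%), and with 28 per arm at 0.5. Sustained group-by-time passes at 0.7. With f = 0.34 entered directly as the interaction effect, power exceeds 99%. Carrying the last observation forward also keeps the nominal number nearer 28 than 23, although it may dilute the effect.
- A reader might infer from the 2,000 IU study cited under Study interventions that 0.68 SD is optimistic. That study differed in dose, duration and population, and no SD is quoted.
- A reader might call the attrition allowance wrong, since 23 / 0.8 = 28.75. The text says 20% is added, and 23 × 1.2 = 27.6 rounds to 28 as stated.

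**Conclusion.** The concern holds in limited form and should be fixed. The 80% figure can be reproduced, but only by supplying a metric, a correlation and a tested effect that the protocol does not state, and the best match is a test other than the one planned for the group effect. For that planned test, ANCOVA corrected for three visits, 0.68 SD and 23 per arm give less than 80% power at correlations up to 0.7, and 91% at 0.8. With all 28 per arm analysed, power is 68% at correlation 0.5 and 86% at 0.7. If 0.34 is a standardised mean difference, power is far below 80% at correlations 0.3 to 0.7, corrected or not.

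These figures rest on compound symmetry, a divisor of 3 and, for group-by-time, a difference that is zero at baseline and constant afterwards. Confidence is moderate on which routine was used. It is high that the section does not demonstrate 80% power for the corrected ANCOVA.

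**What to change.** Reword Sample size calculation in the protocol:
- State whether 0.34 is Cohen's f or a standardised mean difference, which correlation between visits was assumed, and which effect was tested.
- Tie the power statement to the test of quadriceps strength that the sponsor designates as primary, at the alpha actually used, including the Bonferroni divisor if one applies. Which visit and test that is remains the sponsor's decision.
- Replace the 80% claim with the power, or the detectable difference, that 23 and 28 per arm deliver for that test over a plausible range of correlations; the tables above show the form.

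The cost is a text amendment. Recruitment has begun, and no extra patients, visits or measurements are needed. The stated power may become less favourable.

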### Statistical analysis

Data in this study will be analyzed according to the intention-to-treat principle. Only the full analysis set and per-protocol set will be used for primary outcome analysis. The last observation carried forward (LOCF) will be used to impute the missing data by replacing it with the last observed value.

Quantitative variables will be expressed as mean ± standard deviation. Normality tests will be performed to determine whether the data is normally distributed. A one-way analysis of covariance (ANCOVA) tests with Bonferroni correction and with the baseline value as a covariate was conducted at 3m,6m, and 12m to determine the group effect on each parameter. Independent T-test (two-tailed) are used for multiple testing of continuous variables. Whereas the Chi-square test will be used to compare the proportions of categorical variables and to calculate the differences in the count data. A repeated measure analysis of variance (ANOVA) will be used to analyze the trend of changes in the scores among four-time points (Baseline, 3m, 6m, 12m) to determine the group×time effects. Post hoc analysis with Bonferroni correction will be conducted to explore the differences between baseline and 3m, baseline and 6m, 6m and 12m. The statistical analysis will be performed using commercialized statistical software (SPSS, version 29.0, IBM). All statistical significance is defined as P < 0.05.

Additional analyses will include subgroup analyses to estimate treatment effects for both female and male participants, normal BMI and overweight or obese participants.

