### Study interventions

Pirotta and his colleagues found that daily supplementation with 2,000 IU vitamin D3 for 10 weeks in older adults significantly increased knee extension muscle strength by 8–11% but did not reach the statistically significant group difference compared with the placebo group [23]. In another previous study, 50 older adults with vitamin D levels < 20 ng/ml took 4000IU daily vitamin D supplement, and 78% of aged older adults had 25(OH)D levels ≥ 30 ng/mL after 6 months [24]. The doses of 4000 IU vitamin D3 daily have also been reported to be required to achieve plasma 25(OH)D levels associated with lowest disease risk in observational studies in older adults [25]. Vitamin D group will receive 4000 IU/day for six months, modified from the earlier research [23–25]. Subjects will be randomized into 2 study groups: (1) Intervention group: patients receive daily dose of 4000 IU of vitamin D3 supplements. (2) Control group: patients receive placebo. Supplements will be dispensed to participants in baseline and 1^st^ follow-up to increase the subject compliance.

All study capsules, including the placebo, will be manufactured according to Good Manufacturing Practice (GMP) guidelines for quality assurance (see Fig 2). All capsules purchased from SODX Co., Ltd, Osaka, Japan, and patients in the control arm will receive an identical inert placebo provided by the same company. As a placebo will look and taste like vitamin D3, this can ensure the participants are blinded to the treatment. Utilizing a placebo that closely mimics the appearance and flavor of vitamin D3 will effectively blind the participants to their treatment.

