### Outcomes and outcome assessments

The primary outcomes will be muscle strength using quadriceps and hamstring muscle assessments, and the secondary outcomes will be the post-intervention change in muscle strength function from baseline using 5-time chair stand test, sarcopenia assessment by Dual Energy X-ray Absorptiometry (DXA), handgrip strength and 6-meter gait speed test, six questionnaires: Western Ontario and McMaster Universities Osteoarthritis Index (WOMAC), Knee Injury and Osteoarthritis Outcome Score (KOOS), Short-Form 36 (SF-36), International Physical Activity Questionnaire (IPAQ), Nutritional Intake and Sunlight Exposure questionnaire (Questionnaires can be seen in S5 File), and biochemical assays including serum Vitamin D level and myokines. Blood samples will be taken under non-fasting conditions. The serum obtained will be immediately stored at -80°C until analysis.

Outcome assessments of the patients will be performed at baseline (0 month), 3 months and 6months after the commencement of vitamin D supplement, and 6-month after the interventional period.

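### Last observation carried forward puts on-treatment values into the off-treatment 12-month visit, so the 12-month results can be biased in a direction that cannot be predicted

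*Protocol article*

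**What the plan says.** All on this point is in the protocol article.

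- Statistical analysis, missing data: "The last observation carried forward (LOCF) will be used to impute the missing data by replacing it with the last observed value". No other method is named.
- Statistical analysis, principle and sets: "Data in this study will be analyzed according to the intention-to-treat principle", and "Only the full analysis set and per-protocol set will be used for primary outcome analysis". The article does not define the full analysis set. The per-protocol set is a second population, not a way of handling missing values.
- Statistical analysis, tests that use the completed data: an ANCOVA "with the baseline value as a covariate was conducted at 3m,6m, and 12m to determine the group effect on each parameter", a repeated-measures ANOVA for group by time over the four visits, and the contrasts "Post hoc analysis with Bonferroni correction will be conducted to explore the differences between baseline and 3m, baseline and 6m, 6m and 12m".
- Study interventions: "Vitamin D group will receive 4000 IU/day for six months".
- Outcomes and outcome assessments: after baseline, visits are at "3 months and 6months after the commencement of vitamin D supplement, and 6-month after the interventional period". The last visit is thus 12 months after the start and 6 months after treatment ends.
- Sample size calculation: "An additional 20% will be added to account for possible attrition".

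**The concern.** LOCF assumes that a patient's outcome stays fixed from the last visit attended. In this design, treatment stops between the 6-month and 12-month visits. A patient last seen at 6 months and missing at 12 is recorded as if six months without capsules changed nothing. Whether any gain survives stopping is what the 12-month visit is there to show, so the imputation assumes the answer for those patients.

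A second effect acts earlier. A patient lost before 3 months, if kept in the full analysis set, carries the baseline value to every later visit and counts as zero change. That pulls any 6-month effect towards zero.

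Missing visits are likely, and not only because 20% attrition is planned for. The article withdraws patients with significant adverse events, ends participation after unblinding, makes contact after stopping optional for the participant, and excludes only those with surgery scheduled within six months of a twelve-month study. Some of these routes could differ between arms.

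**Working it through.** **The plan's own figures.** G*Power's between-groups repeated-measures test has noncentrality λ = f²·N·m / (1 + (m − 1)ρ). Take f = 0.34, N = 46, m = 4 and ρ = 0.5 (assumed, as the article gives no correlation). Then λ = 0.1156 × 46 × 4 / 2.5 = 8.51 on 1 and 44 df, with power 0.814. This reproduces 23 per group. Adding 20% gives 23 × 1.2 = 27.6, so 28. Attrition of 20% in 56 patients is 11.2, so LOCF would fill about 11 values at 12 months.

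**Assumptions, not document figures.** The article does not say what metric its 0.34 is in. Because it reproduces as Cohen's f, a two-group difference of 2 × 0.34 = 0.68 SD is used as the 6-month effect. The 3- and 12-month effects, the common decline and the dropout patterns are illustrative. Dropout is random within arm. Expected values are arithmetic. Rejection rates come from simulation with 28 per arm, correlation 0.6, and baseline-adjusted ANCOVA on LOCF data.

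**1. All 20% lost after 6 months.** The expected 12-month difference is 0.8·Δ12 + 0.2·Δ6.
- Effect fully gone: 0.8 × 0 + 0.2 × 0.68 = 0.136 SD (truth 0). It is rejected in 9 to 10% of trials, or 7.9% with correlation 0.5, against a nominal 5%.
- Effect halved: 0.8 × 0.34 + 0.2 × 0.68 = 0.408 SD (truth 0.34).
- Change in the effect from 6 to 12 months, full fade: 0.8 × (−0.68) = −0.544 SD (truth −0.68). Every lost patient contributes zero, so the change shrinks by the fraction lost.

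**2. All 20% lost before 3 months, and kept in the full analysis set.** The 6-month difference is 0.8 × 0.68 = 0.544 SD (truth 0.68).

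**3. The same 20% spread evenly, 0.0667 per interval.**
- Effects 0.34/0.68/0.34 at 3/6/12 months: the 12-month difference is 0.8 × 0.34 + 0.0667 × (0 + 0.34 + 0.68) = 0.34 SD, so there is no net bias. The 6-month difference is 0.8667 × 0.68 + 0.0667 × 0.34 = 0.612 SD (truth 0.68).
- Effects 0.34/0.68/0.68: the 12-month difference is 0.8 × 0.68 + 0.068 = 0.612 SD (truth 0.68), so a lasting effect is diluted.

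**4. No treatment effect, both arms declining, unequal loss.** With a fraction p lost evenly over visits:
- Decline of 0.25/0.5/1.0 SD: LOCF lifts an arm's 12-month mean by (p/3)(1.0 + 0.75 + 0.5) = 0.75p. Loss of 30% versus 10% gives 0.225 − 0.075 = 0.15 SD in favour of the arm losing more, with about 10% rejection.
- Decline of 0.15/0.3/0.6 SD: the lift is 0.45p, so 0.135 − 0.045 = 0.09 SD, with about 7% rejection.
- At 6 months under the larger decline, the shift is only 0.25 × (0.30 − 0.10) = 0.05 SD, with 5.3% rejection.

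**5. No treatment effect, equal loss.** The 12-month bias is 0.00 SD and rejection about 5%, with or without the common decline.

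**Comparison.** In simulation under scenarios 1 (full fade) and 4, ANCOVA on observed values alone gave about 0 at 12 months and about 5% rejection.

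**Standard errors.** In the larger-decline case of scenario 4, the average model standard error with LOCF at 12 months was 0.225, against an empirical SD of 0.223.

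**The case against.** The strongest reply is that nothing here is certain. The article gives no trajectory, no split of dropout by time or arm, and no correlation. With evenly spread loss the half-fade example shows no net 12-month bias. With equal loss and no effect the test keeps its level. Even 15% versus 25% loss gives only 6.5% rejection under the larger decline and 5.0% under the milder one. The 6-to-12-month contrast is labelled post hoc and exploratory. LOCF also keeps patients with incomplete follow-up in a repeated-measures ANOVA, which serves the intention-to-treat aim. All of this stands, and it limits the point to a conditional one.

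Three stronger readings may tempt a reader, and the documents do not support them.

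- *LOCF is the trial's sole method.* It is the only one the article names. A statistical analysis plan or full protocol, not shown here, may add sensitivity analyses.
- *The article says these patients decline, so LOCF must favour the arm with more loss.* The Discussion says only that longer waits may worsen pain, functional performance and quality of life. That is conditional and does not mention knee strength, the primary outcome.
- *LOCF makes standard errors too small.* The 12-month model standard error is smaller than with observed data only (0.229 against 0.261 with evenly spread 20% loss and correlation 0.5). But it agrees with the actual spread of the LOCF estimates, so the excess rejection comes from bias.

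The zero-change problem for early losses also depends on the undefined full analysis set. If that set requires a post-baseline value, the problem does not arise.

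**Conclusion.** The point holds in conditional form. The article fixes a method whose central assumption, no change after the last visit, conflicts with a design that stops treatment before the last visit. The muting of the 6-to-12-month change for late losses follows from the method whenever outcomes really do change. Bias in the 12-month group comparison is possible but not inevitable. Under the stated assumptions it runs from dilution of a lasting effect (0.61 for 0.68 SD), through none, to a false difference of 0.09 to 0.15 SD with roughly 7 to 10% rejection. At 6 months the main risk is dilution from earlier losses, down to 0.54 for 0.68 SD in the extreme case.

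Because the sign depends on quantities unknown in advance, LOCF cannot be justified as the cautious choice. Confidence is high on the structural conflict and only moderate on the magnitudes, which are illustrations. This should be changed, but it does not invalidate the trial.

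**What to change.** In the Statistical analysis section, replace LOCF with a likelihood-based mixed model for repeated measures on all observed visits. Use arm-by-visit terms, baseline as a covariate or with a common baseline mean across arms, and unstructured covariance. SPSS 29, already named in the article, can fit it. Multiple imputation is an acceptable alternative. Report the 6-month (end of treatment) and 12-month (six months off treatment) arm contrasts separately. State whether the full analysis set includes patients with no post-baseline value.

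The mixed model assumes that missingness is explained by the observed data, so add a delta-adjusted analysis to show how far departures from that would change the result. LOCF may stay beside it as a sensitivity analysis, but no more.

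Cost: slightly wider intervals than under LOCF, and a protocol amendment. The article requires ethics committee approval before a change is adopted, and notice to participants. Recruitment was still under way when the article was written, and the randomisation code is to be broken only after database lock, so the change can be made while the data are still blinded.
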